### Behavioral Indicators (Before and After the Intervention)

#### 24-Hour Recall

Food intake will be assessed preintervention and postintervention in children in grades 4 to 6 using 2 nonconsecutive 24-hour recalls (24h-R), with the United States Department of Agriculture Automated Multiple-Pass Method [59]. The procedure consists of conducting an individual interview by a dietitian staff member and recording, on paper, the participant’s total food consumption during the day prior to the interview (from the time the individual woke up until the time they went to bed), ensuring that all foods and beverages are included. During the interview, key questions will be asked to stimulate the participants’ memory. To estimate the participant’s daily nutrient intake, recalls will be processed on the ASA24 site by the dietitian staff member, and for dishes not listed on the ASA24 platform, the ingredients will be individually itemized and recorded on the website.

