#### Indicators of Diet Quality

The following dietary quality indicators will be estimated to examine their association with cardiometabolic risk factors at baseline and to assess changes in eating behaviors after the intervention.

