##### Healthy Eating Index

The Healthy Eating Index (HEI) 2024 will be estimated [60]. The overall HEI score will be calculated using the following classification: (1) optimal, with an HEI score greater than or equal to 81; (2) requires improvement, with an HEI score between 51 and 80; (3) poor, with an HEI score less than or equal to 50 [61].

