The age of participants may also limit their responses, since younger schoolchildren find it difficult to express themselves and remember data (ie, quantity of food and time of PA). This could be improved through greater interaction between staff and participants to build trust and facilitate recall of daily activities, enhancing the accuracy of responses. Regarding the self-reported estimates of PA and dietary intake, they depend on short- and long-term memory, showing greater variability compared to other objective measures [85,86]. However, the 3-day physical activity recall and the 24h-R are validated instruments widely used in the child population [87,88]. The use of few repetitions of the 24h-R does not ensure the measurement of between- and within-person variability; however, administering more repetitions could increase the challenges inherent in data collection in children and adolescents, who may have difficulty sharing information about their behaviors and may experience mental burden and stress [89]. Another limitation is that other important social actors in the student’s life, such as parents, will not be involved; however, the involvement of teachers, and especially classmates, is possible. The curriculum implementation depends on the time available in the school curriculum itself; however, if the intervention begins alongside the school year, it optimizes time and makes it easier to complete it. Another opportunity for future studies is to include other crucial variables such as quality of life and self-esteem, which are important at this stage. Concerning multilevel models, these require larger sample sizes, involve more complex assumptions, and may be sensitive to model misspecification. However, these are well suited for group-randomized trials, as they account for data grouping, provide valid standard errors, accommodate missing or unbalanced data, and allow the simultaneous examination of individual- and group-level effects, thereby improving statistical efficiency and inference.

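### Diet scores from two 24-hour recalls enter the baseline regressions and the HEI classes with no allowance for day-to-day variation, although the two recalls would allow a correction

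*Protocol article*

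**What the plan says.** The 24-Hour Recall section fixes the measurement: "Food intake will be assessed preintervention and postintervention in children in grades 4 to 6 using 2 nonconsecutive 24-hour recalls (24h-R". It adds that "recalls will be processed on the ASA24 site by the dietitian staff member", but does not say how the two days are combined into one value per child.

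The Indicators of Diet Quality section gives the indicators two uses: "to examine their association with cardiometabolic risk factors at baseline and to assess changes in eating behaviors after the intervention". The Healthy Eating Index section then sets classes: "optimal, with an HEI score greater than or equal to 81", "poor, with an HEI score less than or equal to 50", and a middle class of 51 to 80.

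Under Statistical Analysis, specific aim 1 regresses anthropometrics and blood pressure on behavioral variables that include dietary intakes. The model is set out in some detail: a univariate screen at P<.2, forward stepwise selection at P≤.05, sex interactions, a variance inflation limit of 10, and residual plots. No step deals with error in the predictors. HEI and dietary intakes are also continuous outcomes in the arm comparison of specific aim 3.

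The Discussion states the limitation, "The use of few repetitions of the 24h-R does not ensure the measurement of between- and within-person variability", and answers it with the burden that more recalls would place on children and with the validation of the instrument.

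**The concern.** A score built from two days of eating is a child's usual diet plus day-to-day noise. As a predictor, a noisy score gives a slope that is too small when it stands alone, and it can hand part of its effect to correlated predictors when it does not. Against fixed cut-offs, noise widens the distribution and so moves the share of children beyond each cut-off.

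The Discussion treats this as a limit that only more recall days could lift. Two days are indeed too few for a precise value for each child. They are enough to estimate the two variance components for the group, and that is all a correction of slopes and class shares requires.

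At stake are the baseline associations of diet with adiposity and blood pressure, and any reported percentages of children with an optimal or poor diet. Selection by P value adds to the problem, because a diet variable with a weakened association is more likely to be dropped.

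**Working it through.** The article gives no variance, reliability or power figure for diet, so there is no stated number to reproduce.

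**Inputs.** From the article: two recalls per child per occasion, cut-offs 50 and 81, 451 children in total. Assumed, because not given: within-to-between variance ratio r from 0.5 to 4; true HEI mean 42 to 65.5 and between-child SD 6 to 10; 150 or 225 children in grades 4 to 6 (225 is about half of 451). Errors are taken as random, and distributions as normal.

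**1. Slope on one diet predictor.** A two-day mean has variance B + W/2, with B between-child and W within-child variance. The expected slope is the true slope times λ = 1/(1 + r/2):

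| r | 0.5 | 1 | 2 | 3 | 4 |
|---|---|---|---|---|---|
| λ | 0.80 | 0.67 | 0.50 | 0.40 | 0.33 |

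A sum of the two days only rescales the mean. Using one day alone is worse: 1/(1 + r) runs from 0.67 to 0.20 over the same range.

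**2. Detecting an association.** A true correlation of 0.20 becomes 0.20 × √λ = 0.163, 0.141 and 0.115 for r = 1, 2 and 4. By the Fisher transformation with n = 225 and two-sided 5%, power is Φ(atanh(ρ) × √222 − 1.96). It falls from 86% to 69%, 56% and 41%.

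**3. Two correlated diet predictors.** Take true correlation 0.6, true slopes 1 and 0, unit true variances, r = 2 for both, and independent errors. The observed variances are 2 and the observed covariance 0.6, so the determinant is 4 − 0.36 = 3.64. The fitted slopes are (2 × 1 − 0.6 × 0.6)/3.64 = 0.45 and (2 × 0.6 − 0.6 × 1)/3.64 = 0.165. The predictor with no effect acquires one.

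**4. HEI classes.** The observed SD is the true SD × √(1 + r/2). Boundaries between whole scores are taken at 50.5 and 80.5. With a between-child SD of 8:

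| True mean | Poor, true | Poor, observed (r = 1 / 2 / 4) | Optimal, true | Optimal, observed (r = 1 / 2 / 4) |
|---|---|---|---|---|
| 45 | 75.4% | 71.3 / 68.7 / 65.4% | about 0% | 0.015 / 0.085 / 0.52% |
| 50.5 | 50.0% | 50.0 / 50.0 / 50.0% | 0.009% | 0.11 / 0.40 / 1.52% |
| 55 | 28.7% | 32.3 / 34.5 / 37.3% | 0.07% | 0.46 / 1.21 / 3.29% |
| 60 | 11.8% | 16.6 / 20.1 / 24.6% | 0.52% | 1.82 / 3.50 / 6.95% |

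SDs of 6 and 10 give the same directions.

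**5. Whether two recalls suffice for a correction.** In a simulation (4,000 runs, true slope 0.30, n = 225), the uncorrected slopes were 0.20, 0.15 and 0.10 for r = 1, 2 and 4. Dividing by the λ estimated from the two replicates gave medians of 0.30 each time. The SD of the estimated λ was 0.05, 0.07 and 0.09 at n = 225, and 0.06, 0.08 and 0.11 at n = 150. The correction works, with less precision when r is large.

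**The case against.** The strongest reply is that the premise is partly silence. The article does not say that the two days are averaged, nor that the result is called usual intake, and a condensed article may leave such handling to the full protocol or analysis plan. The limitation is openly disclosed, and its wording is cautious. It does not rule out a correction. The HEI classes may be descriptive only, since no model under Statistical Analysis is said to use them, and HEI is already a continuous outcome there. The Introduction words specific aim 1 around psychosocial, family and perception variables, so diet as a predictor is only one part of it.

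Much of this stands and limits the point. Averaging is an inference. But any score per child taken directly from the two days carries day-to-day error, and a plain mean is milder than using one day. The article also does more than stay silent: it specifies the aim 1 model closely without such a step, and it argues in the Discussion as though more recall days were the only answer. Validation of the instrument does not remove variation between days.

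A reader might also infer that both extreme HEI classes are inflated. The documents give no HEI mean or SD, and the share labelled poor falls if the true mean is below about 50. Nor can one say that every diet association shrinks: that is certain only for a single error-prone predictor.

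**Conclusion.** The point holds in a limited form. Followed as written, the plan yields distorted diet slopes at baseline and distorted HEI class shares in grades 4 to 6, and the planned data would allow both to be corrected.

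For r between 0.5 and 4, a single-predictor slope loses 20% to 67% of its size. In multivariable models the distortion can also fall on correlated predictors. The optimal share is overstated in every case computed; the direction for the poor share depends on which side of about 50 the true mean lies. All sizes rest on assumed variances, means and sample sizes, and on random day-to-day error.

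It would be wrong to read this as a flaw in the randomized comparison. Random day-to-day error in a continuous outcome costs precision but does not bias the difference between arms.

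**What to change.** - Keep the recall days as replicates and report the estimated within-child and between-child variances.
- For the baseline diet associations in grades 4 to 6, report regression-calibrated slopes beside the uncorrected ones for the final model. Their intervals should reflect that the calibration factor is itself estimated, for example by a bootstrap that repeats both steps. Calibrate several diet variables jointly.
- Give the shares at or below 50 and at or above 81 from an estimated usual-intake distribution, not from individual two-day scores.
- Reword the Discussion: two recalls are too few for precise individual values, but they allow a group-level correction for random variation.

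No new data are needed, and Table 3 shows analysis marked complete for only two of the four schools. The costs are some analyst time and wider intervals. The correction relies on day-to-day error being random. It does not remove systematic misreporting by children, and it does not recover the power lost when weakened diet variables are screened out. The arm comparison of continuous HEI and intakes can stay as it is.

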### Study Design

The study design is a randomized controlled trial in which school groups (classrooms) will be randomized either to the intervention or control arm. Baseline measurements will be completed before group assignment, reducing the potential for selection bias. The randomization sequence will be generated using a computerized random number generator (IBM SPSS Statistics version 21.0) by a researcher not involved in the study. Classroom groups will be paired within each school and randomly assigned (1:1) to the intervention or control arm. Allocation will be revealed by the independent researcher only after baseline measurements are completed and the intervention curriculum has been designed. The study will be conducted over 1 year in 4 phases. In the initial diagnostic phase (phase 1), baseline obesity risk factors will be measured in both control and intervention arms, assessing family and sociodemographic variables (family interaction, diet quality at home, body image perception [BIP], and psychosocial well-being) and schoolchildren’s health variables (anthropometry, diet, and blood pressure). Parents in both arms will receive a report on their child’s diagnosis, and in the control group, some recommendations will be added to improve their health and eating habits. Phase 2 consists of implementing the curriculum during 4 months in the intervention arm. Phase 3, at the end of the intervention, consists of the evaluation of results from the intervention arm in terms of knowledge acquisition, effectiveness, retention, motivation to change, fidelity, and acceptability by schoolchildren; in both arms, changes in knowledge, anthropometrics, blood pressure, and behavior of schoolchildren in terms of diet quality, exercise practice, and sleep quality will be measured. Finally, in phase 4, after 6 months of the intervention, sustained changes in anthropometrics and behavior (same measurements as phase 1) will be measured. The study design is shown in Figure 1. The program will allow for ongoing contact with participants, thereby promoting their retention and measuring immediate and medium-term outcomes. Participants in the control group will receive a summary version of the intervention in the next school year.

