### Selection of Schools

The districts and neighborhoods with the lowest economic resources in the region were identified using socioeconomic census data from the National Institute of Statistics and Geography (INEGI, for its acronym in Spanish), and 4 elementary schools were selected according to logistical feasibility and resources: 1 in Loma de Bácum (representing the rural area) and 3 in Ciudad Obregón, Sonora, México (representing the urban area). An interview will be held with the school principals to present the proposal, and those who agree will be asked for written authorization. Within each school, an equal number of groups (classrooms paired by grade) will be selected for the intervention and control arms, allowing for approximate matching of participants by sex and age in each arm. This approach allows us to offer the program to at least half of the students in each school and to implement the intervention in as many schools as possible according to available resources.

The number of classrooms per school is determined by the existing school structure and logistical feasibility. Across the 4 schools, a total of 24 classrooms will be included (12 in the intervention arm and 12 in the control arm), with varying numbers of students (participants) per classroom, since student grouping is pre-established by the Ministry of Education at the beginning of the school year.

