### Statistical Analysis

The normal distribution of the data will be verified using skewness, kurtosis, and Kolmogorov-Smirnov tests. Quantitative data with nonnormal distribution will be mathematically transformed for parametric analysis, or alternatively, nonparametric analysis will be used. Means and SDs will be calculated for continuous variables and percentages for categorical variables. To test age, sex, socioeconomic status, and location baseline differences, we will use chi-square tests for qualitative demographic variables (eg, socioeconomic level, family medical history, sport practice, etc) and analysis of covariance for quantitative variables (eg, anthropometrics, dietary intakes, HEI, TMexD, sleep time, BIP, family interaction, and psychosocial well-being). To evaluate specific aim 1, potential baseline associations of dependent variables (eg, anthropometrics and blood pressure) with independent behavioral variables (eg, dietary intakes, exercise and sleep time, family interaction, psychosocial well-being, and perception of childhood obesity) will be tested using multiple linear regression, starting with univariate regression (*P*<.2 and biological plausibility). Models will be built by a combination of univariate analysis and forward stepwise model selection using *P*≤.05 and biological plausibility. Preliminary models will be assessed for possible interactions (*P*≤.1) between sex and other variables included in the model, for collinearity (variance inflation factor<10), and for linear regression assumptions (linearity, normality, and homoscedasticity) using residual plots. Specific aim 2 will use mixed methods (qualitative and quantitative) to analyze results in terms of retention, fidelity, and acceptability of the intervention by children and school administrators. Specific aim 3 will compare the changes between the experimental arms (intervention vs control) from baseline to postintervention and to the 6-month follow-up in anthropometrics, blood pressure, HEI, dietary intakes, PA, sleep time, and knowledge. Primary analyses will follow the intention-to-treat principle. Given the hierarchical structure of the data (students nested within classrooms and classrooms within schools) and the repeated measurements over time (baseline, postintervention, and 6-month follow-up), intervention effects will be evaluated using multilevel mixed-effects regression models. Due to the cluster-based allocation, the intraclass correlation will be considered, potential attrition will be monitored, and all analyses will account for clustering to provide valid inferences. Models will include fixed effects for study arm, time, and the arm×time interaction, and random effects for classroom and school to account for intracluster correlation. Baseline values of the outcomes and covariates will be included as appropriate. Effect estimates with 95% CIs will be reported. We will examine model assumptions and fit indices. SPSS (IBM SPSS Statistics version 21.0) and STATA (StataCorp version 14.0) software will be used, with a *P* value <.05 for all statistical analyses.

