
## Results

From October 2023 to August 2024, a total of 451 participants were recruited from 4 different elementary schools in Sonora, México. As of February 2026, the collected data are in the process of analysis and interpretation. Table 3 presents the current status of each stage of the protocol as of February 2026.

**Table 3. T3:** Current status of the research protocol.

	Participating schools			
	Nueva Creación (26EPR0373T^a^)	Miguel Hidalgo (26DPR1013P^a^)	Héroe de Nacozari (26DPR0251J^a^)	Gral. Plutarco Elías Calles (26DPR0250K^a^)
Training and program design	✓	✓	✓	✓
Selection of participating schools	✓	✓	✓	✓
Sample size, n	173	117	86	75
Initial measurements	✓	✓	✓	✓
Intervention	✓	✓	✓	✓
Final measurements	✓	✓	✓	✓
Follow-up (measurements at 6 months)	✓	✓	✓	✓
Date capture	✓	✓	✓	✓
Data analysis	✓	✓		
Data interpretation				

a Work Center Code of the primary school.

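### Multilevel models are credited with valid standard errors without qualification, but only 24 classrooms (12 pairs) are randomized; inference should be tied to those units

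*Protocol article*

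**What the plan says.** Allocation is by classroom. Under Study Design, "Classroom groups will be paired within each school and randomly assigned (1:1) to the intervention or control arm". Under Selection of Schools, "a total of 24 classrooms will be included (12 in the intervention arm and 12 in the control arm". Pairing is by grade within school, so there are 12 pairs. The Results section reports that "a total of 451 participants were recruited from 4 different elementary schools".

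For aim 3, the Statistical Analysis section specifies: "Models will include fixed effects for study arm, time, and the arm×time interaction, and random effects for classroom and school". It adds that "all analyses will account for clustering to provide valid inferences", that "Effect estimates with 95% CIs will be reported", and that testing is done "with a *P* value <.05 for all statistical analyses". It names SPSS and Stata, but no estimator (ML or REML), reference distribution or degrees-of-freedom method.

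The Discussion concedes that multilevel models need larger samples and can be sensitive to misspecification. It then calls them well suited to group-randomized trials, "as they account for data grouping, provide valid standard errors, accommodate missing or unbalanced data".

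**The concern.** The Discussion meets a small-sample caveat with a property that the models have only when the number of randomized units is large. The information on the arm contrast comes from 24 classrooms, not from 451 children. That leaves 24 − 2 = 22 degrees of freedom, 19 after school effects, or 11 if the pairs are respected. At that size, a mixed model with a classroom term does not by itself give a nominal 5% test: the normal critical value is too small, and ML also underestimates the classroom variance. The Discussion does concede a low sample size, but in terms of participants, so the number of classrooms is never named as the constraint.

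The stake is the error rate and CI coverage behind every effectiveness statement under aim 3. It is greatest for 24-hour recall and physical activity recall, which are collected only in grades 4 to 6 and so come from fewer classrooms.

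**Working it through.** **Inputs.** From the article: 24 classrooms, 12 per arm, 12 pairs; 451 children (451/24 = 18.8, taken as 19 per classroom); 5% level, taken as two-sided; three time points. Assumed, because not given: ICC 0 to 0.20; 12 classrooms for outcomes limited to grades 4 to 6. The 5% level is itself an input, so there is no derived figure to reproduce. The question is what a nominal 5% test delivers.

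**Step 1: analytic size of a z test.** If the statistic follows t on df degrees of freedom but is compared with 1.960, its size is 2·P(t_df > 1.960).

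| df | Source | Size | CI coverage | t critical value | t / 1.960 |
|---|---|---|---|---|---|
| 22 | 24 − 2 | 6.3% | 93.7% | 2.074 | 1.06 |
| 19 | 24 − 4 schools − 1 | 6.5% | 93.5% | 2.093 | 1.07 |
| 11 | 12 pairs − 1 | 7.6% | 92.4% | 2.201 | 1.12 |

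**Step 2: simulated size with classroom variance on the arm contrast.** 400,000 null trials per setting, equal classrooms of 19, one summary per child, classroom random intercept.

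| Classrooms | ICC | ML, z | REML, z | REML, t (22 df) |
|---|---|---|---|---|
| 24 | 0.02 | 6.4% | 5.6% | 4.4% |
| 24 | 0.05 | 7.2% | 6.1% | 4.9% |
| 24 | 0.10 | 7.3% | 6.3% | 5.0% |
| 12 (assumed) | 0.02 | 7.1% | 5.9% | – |
| 12 (assumed) | 0.05 | 9.1% | 7.1% | – |
| 12 (assumed) | 0.10 | 10.1% | 7.7% | – |

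A second simulation (4,000 trials per ICC) used the school totals 173, 117, 86 and 75, with 10, 6, 4 and 4 classrooms per school assumed.
- REML with z: 4.3% at ICC 0, 4.9% to 5.2% at 0.01, 5.7% at 0.03, 5.9% to 6.1% at 0.05, and 6.5% to 6.6% at 0.10.
- ML with z, no school effects: 4.8% at ICC 0, rising to 7.6% at 0.10.
- ML with z and fixed school effects: 5.0% at ICC 0, rising to 9.7% at 0.10.
- REML with t: 3.2% to 5.3% for ICC 0 to 0.20.

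So the excess depends on the reference, the estimator and the ICC, and is absent near ICC 0.

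**Step 3: the arm×time test with random intercepts only.** With complete balanced data, a change from baseline is a within-classroom difference, so the classroom intercept cancels. The contrast is then tested against residual variation. There are 24 × 19 × 3 = 1,368 observations, less 6 fixed-effect parameters and 22 for classrooms within arm, which leaves 1,340 df. The t critical value is then 1.962, practically the normal one, so a degrees-of-freedom correction changes almost nothing.

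Simulated size of this test (z reference, 5,000 trials per setting), by classroom-by-time variance share and within-child correlation:

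| Classroom-by-time share | Correlation 0.5 | Correlation 0.8 |
|---|---|---|
| 0 | 0.5% | under 0.1% |
| 0.01 | 2.2% | 0.2% |
| 0.03 | 6.1% | 2.7% |
| 0.05 | 9.7% | 6.6% |

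The error can go either way. In the same runs, a t test on classroom mean changes (22 df) gave 4.4% to 5.5%.

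**Step 4: inference on the pairs.** A paired t test on 12 differences has 11 df and does not depend on the random-effects structure or a software default. In simulation with 24 classrooms it held 4.5% to 5.4% in every setting run. A re-randomization test has 2^12 = 4,096 within-pair allocations, ample for a 5% test.

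**The case against.** A reader might infer that the article plans large-sample tests, and hence that its false positive rate is above 5%. The documents do not support that. The Statistical Analysis section names no reference distribution and no estimator, and an REML analysis with small-sample t tests would fit its wording equally well. These choices are commonly left to an analysis plan, which is not shown, so their absence is not an error.

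Three further points stand. There is no meaningful excess under REML at ICC 0 to 0.01, and at higher ICC it is about one percentage point. The 7% to 10% figures for 12 classrooms stack ML, a z reference and an assumed classroom count. And in the model as literally written, even the direction of the error is not settled (Step 3), so a categorical claim of inflation fails.

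It is also fair that the Discussion carries a caveat about sample size. But the caveat is immediately answered by the unqualified statement about standard errors. That statement is printed in the article and is not a detail deferred elsewhere. With 24 classrooms it holds only for analyses built on the classrooms.

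**Conclusion.** The point holds in conditional form. The Statistical Analysis and Discussion sections present multilevel models as giving valid inference without reference to the 24 randomized classrooms. If a z reference is used and classroom variance bears on the arm contrast, two-sided error is about 6% with REML and about 6.5% to 7.5% with ML at ICC 0.02 to 0.10. It can be higher with ML plus school effects, or with about 12 classrooms. ICC, equal classroom sizes, classrooms per school and the 12-classroom figure are assumptions. What is established is an unqualified claim that needs a condition, and a better-protected analysis at low cost; actual inflation in this trial is not established. The change is worth making while analysis is unfinished: the status table marks data analysis for two of the four schools and interpretation for none.

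**What to change.** In Statistical Analysis, base aim 3 inference on the randomized units: a paired t test on the 12 classroom-pair differences (11 df), or a re-randomization test over the within-pair allocations.

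Alternatively, fit by REML with Kenward-Roger or Satterthwaite degrees of freedom, in a model whose classroom variance bears on the tested contrast. That means either a classroom-by-time random term, or baseline-adjusted follow-up values with a classroom effect. Adding the correction to the intercepts-only arm×time model would not be enough.

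In the Discussion, limit the statement on valid standard errors to analyses with such a correction, and name the number of classrooms as the limiting sample size.

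The cost is a few sentences and wider intervals: about 6% at 22 df (2.074/1.960) and 12% at 11 df (2.201/1.960), so some borderline results will lose significance. For outcomes limited to grades 4 to 6 the price is higher. If they come from 12 classrooms in 6 pairs, the paired test has 5 df (2.571/1.960, about 31% wider). The 2^6 = 64 allocations then give a smallest two-sided P value of 2/64 = 0.031.
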